### Statistical considerations

Immediate discharge (Intervention) is compared with discharge after 24-h in-hospital observation with rhythm monitoring (Comparator). We chose a prospective analysis due to the patient and physician bias, which would be inherent to a retrospective design. By application of 5-day ambulant Holter monitoring for all participants, we are able to compare all (non-)fatal events in both arms for which admission is strictly not mandatory (e.g. nonrhythm issues and/or later timing of nonfatal diagnoses). Based on studies on low- and intermediate-risk syncope patients in the setting of ED and in line with data from our own institute, we anticipate an event rate of 18% in both arms.^14,18–33^ By noninferiority, we aim to show that immediate discharge of these low-/intermediate-risk syncope patients is feasible and safe. With a noninferiority limit of 9% (for the difference in event rates, 50% of 18%), inclusion of a total of 640 patients with a one-sided type-1 error of 0025 provides the trial with 80% power (10% loss included). In the RISC trial, the noninferiority margin for the risk difference was set at 9% against an expected event rate of 18%, or half of the expected event rate. This margin is equivalent to a noninferiority margin of 1.50 for relative risk. The RISC trial’s noninferiority boundary is consistent with choices made for major landmark RCTs that influenced current guidelines (examples of RCTs are available upon request). In general, the choice of the noninferiority boundary has a major impact on the sample size needed for adequate power. A stricter noninferiority boundary would necessitate an impractically large sample size. For example, a noninferiority margin of 6% against an expected event rate of 18%, equivalent to a relative risk margin of 1.33, would more than double the sample size to 2 × 644. For the inclusion rate, based on the reference areas of the participating hospitals, the annual admissions of syncope on the emergency department, this will result in ≈ 50 eligible patients per year per centre.

### Data analysis and bias

The main analysis is designed to evaluate whether immediate discharge (investigational treatment strategy) is noninferior to 24-h admission with continuous rhythm observation (reference treatment strategy) with respect to the primary composite endpoint of fatal and nonfatal events. The occurrence of the composite primary endpoint will be analysed in a statistical comparison of two proportions of (non-)fatal events. Rates of the primary endpoint are calculated as the proportion of patients in whom the primary endpoint has occurred. Rate differences are defined as the rate under the investigational treatment strategy minus that under the reference treatment strategy. The 95% confidence interval for the rate difference is calculated according to the Farrington–Manning method. Noninferiority of the investigational strategy of immediate discharge will be declared if the 95% confidence interval for the rate difference excludes 9%. Use of 95% confidence interval is equivalent to noninferiority testing with a one-sided type I error (α) of 2.5%. The one-sided *P* value for testing noninferiority with a margin of 9% is calculated according to Farrington–Manning method and must < 2.5% for rejection of the null-hypothesis of inferiority.

All of the analyses are carried out in the population of all randomized patients under application of the intention-to-treat principle, which implies that all primary endpoints are counted irrespective of the implementation of the randomized treatment assignment.

The follow-up period for each patient begins on the day of randomization and will be as long and continues for up to 12 months, with the aim of complete data collection. It is expected that the occurrence of the primary endpoint at 24 h will be known for all patients, except for those patients with early discontinuation of follow-up because of full withdrawal of informed consent.

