### Baseline characteristics

For comparison of the groups, baseline characteristics will be collected; these entail the following: age, height, weight, country of birth, number of TLOCs within the last year, smoking, alcohol use, drug use, medication use, frailty, comorbidities, most probable diagnosis, and low-risk, high-minor, and high-major criteria.^1^

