### Endpoints

The primary safety endpoint consists of the composite of arrhythmia disorders (supraventricular tachycardia, sinus pauses or bradycardia, and ventricular tachycardia), pre-defined conduction disorders (second- or third-degree AV block), syncope recurrence, unexplained falls with injury, all-cause death, and cardiovascular death (Appendix B) at 24 h after randomization. All primary endpoints will be evaluated at 24 h. Subgroup analysis will be performed on the low-risk and intermediate-risk–only cohorts.

Secondary endpoints include clinically relevant diagnostic yield of Holter monitoring, total admission costs, number of syncope-related tests and consultations after 1 month, duration of in-hospital stay after randomization for both treatment arms (superiority), and differences in proportion of correct diagnoses in both arms. In addition, quality of life and societal costs are assessed using telephone consults and standardized questionnaires of the SF12, SDF, EQ-5D-5L, and study-adapted iMCQ and iPCQ (Appendix A). Although quality of life (measured as QALYs) may not differ due to the risk of the population closely resembling a normal population, there might be a difference in perceived safety and understanding affecting the quality of life indirectly.

All primary endpoint definitions are described in Appendix B. A critical event committee centrally reviews all events that are potential endpoints.

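### The unadjusted primary risk difference is valid and adequately powered, but it leaves out risk class and age, which are already collected, and so gives up a little precision

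*Protocol article*

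**What the plan says.** The section Data analysis and bias sets out the whole primary analysis: "The occurrence of the composite primary endpoint will be analysed in a statistical comparison of two proportions of (non-)fatal events". It continues: "The 95% confidence interval for the rate difference is calculated according to the Farrington–Manning method". A one-sided P value from the same method is tested at 2.5% against a 9% margin. No covariate or stratum is named.

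Two kinds of baseline information are available for every patient:

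- **Risk class.** The sections Patient selection and Risk stratification have patients scored as low or intermediate risk at screening. High-risk patients are excluded.
- **Age and other characteristics.** Under Baseline characteristics: "For comparison of the groups, baseline characteristics will be collected". The list includes age, frailty, comorbidities and the individual risk criteria.

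In the analysis, risk class appears only under Endpoints: "Subgroup analysis will be performed on the low-risk" and intermediate-risk cohorts.

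On size, the section Statistical considerations says "we anticipate an event rate of 18% in both arms". It sets the margin at 9 percentage points and states that "inclusion of a total of 640 patients" gives 80% power at one-sided 0.025 with 10% loss included.

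**The concern.** The primary analysis is described completely enough that the choice of an unadjusted estimate is made in the article itself, not left to a separate analysis plan. If risk class or age predicts the composite, a standardised risk difference targets the same marginal quantity, keeps the 9% margin, and has a variance that is no larger in large samples. It needs no extra patients or data.

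Precision matters to this sponsor. The section Statistical considerations defends the 9% margin partly because a stricter one would need an impractically large trial. What is at stake is a slightly wider interval than necessary, in a trial decided by whether one confidence limit lies below 9%.

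**Working it through.** **Inputs from the Protocol article:** event rate p = 0.18 in both arms; margin 0.09; one-sided α 0.025 (z = 1.960); power 80% (z = 0.842); 640 patients randomised 1:1; 10% loss.

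**Reproducing the stated size (unpooled variance).**
n per arm = 2p(1−p)(1.960 + 0.842)² / 0.09² = 0.2952 × 7.849 / 0.0081 = 286.05, so 287 per arm and 574 in total. Allowing for loss, 574 / 0.9 = 638, against 640 stated. The figure reproduces for the unadjusted analysis.

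**Power as planned.** 640 less 10% is 576, or 288 per arm.
SE = √(0.2952 / 288) = 0.03202.
Power = Φ(0.09 / 0.03202 − 1.960) = 80.3%.
Half-width = 1.960 × 0.03202 = 6.27 points.
For the Farrington–Manning test itself, the normal approximation gives 79.7% and exact enumeration 79.9%.

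**Power if all 640 are evaluable (320 per arm).** SE = √(0.2952 / 320) = 0.03037, and power is 84.2% (83.7% Farrington–Manning approximation, 83.9% exact).

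**Effect of adjustment.** Let R² be the share of outcome variance explained by the baseline covariates. The variance of the standardised risk difference is about 2p(1−p)(1−R²)/n. The article gives no event rate by risk class or age, so R² is an assumption. One illustration: classes with rates of 12% and 24%, split 50:50, give R² = 0.06² / (0.18 × 0.82) = 0.0036 / 0.1476 = 0.024.

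| R² (assumed) | Power, 288 per arm | Half-width, 288 per arm (points) | Power, 320 per arm |
|---|---|---|---|
| 0 (as planned) | 80.3% | 6.27 | 84.2% |
| 0.024 | 81.2% | 6.20 | 85.1% |
| 0.05 | 82.2% | 6.1 | 86.0% |
| 0.10 | 84.2% | 6.0 | 87.8% |

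Each entry is Φ(0.09/SE − 1.960) or 1.960 × SE, with SE = √(0.2952(1−R²)/n).

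The gain does not depend on the variance formula. Scaling the Farrington–Manning approximation to an effective 288/(1−R²) per arm takes 79.7% to 81.7% at R² = 0.05 and to 83.7% at R² = 0.10.

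**Risk class alone.** The overall rate is held at 18% and 30% to 70% of patients are assumed to be intermediate risk:

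| Odds ratio, intermediate v low (assumed) | R² | Power, 288 per arm |
|---|---|---|
| 1.5 | about 0.005 | 80.4–80.5% |
| 2 | 0.012–0.017 | 80.7–80.9% |
| 3 | 0.026–0.045 | 81.3–82.0% |
| 5 | 0.044–0.096 | 82.0–84.1% |

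**Expressed as patients.** The number per arm for 80% power falls from 287 to 272 at R² = 0.05 and to 258 at R² = 0.10.

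**The case against.** The strongest reply is that nothing here is wrong. The crude comparison is valid under randomisation, and the estimand, margin, test and sample size agree with one another. Adjustment is a choice, its benefit is assumed, and adopting it changes a published primary analysis while the trial is enrolling. All of this stands. It limits the point to efficiency but does not remove it, because the adjusted estimate answers the same question against the same margin.

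Four stronger readings are tempting and are not supported:

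- **That the trial has only 80% power and nothing in hand.** The 80% is after 10% loss. The section Data analysis and bias expects the 24-hour endpoint to be known for all patients except full withdrawals of consent. Complete data would give about 84% without adjustment, the same as R² = 0.10 at 288 per arm.
- **That randomisation ignores risk class.** The Randomization section names no stratification factor, but a condensed article may leave this to the full protocol. Silence does not show that there is none.
- **That chance imbalance in the risk mix distorts the crude result.** Such imbalance is ordinary sampling error, which the confidence interval already covers. In the 12% v 24% illustration, one standard deviation of imbalance is √(2 × 0.25 / 288) = 4.2 points in the intermediate share. That moves the rate difference by 0.042 × 12 = 0.5 points.
- **That the score is known to predict this endpoint.** It grades the risk of serious cardiovascular events. Appendix B also counts premature-beat doublets, bigeminy, non-sustained atrial runs and near-syncope. The intermediate class also takes in patients with no score points but a high burden feature. Risk class may therefore be only weakly prognostic here.

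**Conclusion.** The point holds as a modest, nearly free improvement. The primary analysis is correct and its sample size reproduces. It forgoes whatever precision risk class and age could supply.

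For R² between 0.024 and 0.10, that is about 1 to 4 points of power and about 0.1 to 0.3 points of half-width at 288 per arm. With risk class alone and an odds ratio of 2 or less, it is under 1 point of power. These sizes rest on the planned 18% rate, a large-sample variance formula, and a prognostic strength that the article does not document. If the covariates turn out not to be prognostic, almost nothing is gained and, asymptotically, nothing is lost.

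**What to change.** Before any unblinded outcome data are seen, amend the plan as follows:

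- **Primary estimate:** the marginal risk difference (immediate discharge minus 24-hour observation), standardised over all randomised patients from a logistic model with arm, risk class (low/intermediate) and age. Fix the form in which age enters.
- **Inference:** a robust or delta-method 95% confidence interval, with noninferiority declared if its upper limit is below the same 9% margin. Take the one-sided P value from the same estimate and standard error, so that test and interval agree.
- **Sensitivity analysis:** the unadjusted Farrington–Manning interval and P value, as now described.

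The model has three terms besides the intercept if age enters linearly, against about 0.18 × 576 = 104 expected events, so it is not demanding.

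The cost is a documented and dated amendment to the published primary analysis, plus a few lines of code. No new data, patients or change of margin are needed. The Summary states that the trial is still enrolling, so the change can still be made.

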## Summary

Syncope is a common symptom with a broad differential diagnosis, high prevalence, and substantial health care costs. Current guidelines on syncope recommend discharging patients with a low risk of serious cardiovascular events; however, the optimal timing for discharge of low- and intermediate-risk patients is not defined in the guidelines. In current medical practice, low- and intermediate-risk syncope patients are either discharged immediately or discharged after 24 h in-hospital rhythm monitoring (telemetry). We propose a randomized clinical trial comparing immediate discharge (the intervention) with discharge after 24 h rhythm observation (the comparator) in pre-defined syncope patients classified as low or intermediate risk according to the risk features in the ESC guideline on syncope. The RISC trial aims to determine if admission for 24 h in hospital rhythm observation can be safely omitted, potentially reducing health care costs while improving care for syncope patients. This multicentre trial is currently enrolling patients across 10 teaching hospitals throughout the Netherlands.

## Data Availability

The data underlying this article cannot be shared publicly due to protection of patient privacy and confirmation to GDPR standards. Completely anonymized data will be shared on reasonable request to the corresponding author with approval of the medical ethical board.

## Appendix A Follow-up scheme

**Table oeag078-ILT1:**

	**QUESTIONNAIRES**	**DIRECT CONTACT**
**ENROLLMENT**	Study specific questions + SF-12 + SDF + EQ-5D-5L	An vivo
**DAY 1**	EQ-5D-5L	Telephone
**DAY 2**	EQ-5D-5L	—
**DAY 3**	EQ-5D-5L	—
**DAY 4**	EQ-5D-5L	—
**DAY 5**	EQ-5D-5L	—
**DAY 6**	EQ-5D-5L	—
**DAY 7**	EQ-5D-5L + Holter specific questions	Telephone
**END WEEK 2**	EQ-5D-5L	—
**END WEEK 3**	EQ-5D-5L	—
**1 MONTH**	Study specific questions + SF-12 + SDF + EQ-5D-5L + iMCQ + iPCQ	Telephone
**1 YEAR**	Study specific questions + SF-12 + SDF + EQ-5D-5L + iMCQ + iPCQ	Telephone

## Appendix B Study parameters / primary outcomes:

*Supraventricular tachycardia:*

- Any atrial tachycardia (sustained or non-sustained ≥ 3 consecutive complexes)
- Atrio-Ventricular Nodal Re-entry Tachycardia (AVNRT) or Atrioventricular Re-Entry Tachycardia (AVRT)
- Premature Atrial Complex (PAC): >2 doublets or >2 episodes of 3 s duration of bi- or trigemini and/or >5%
- Atrial Fibrillation *de novo*

*Ventricular tachycardia:*

- Any Ventricular Tachycardia (sustained/non sustained)
- Ventricular Fibrillation
- Premature Ventricular Complexes: >2 doublets or >2 episodes of 3 s duration of bi- or trigemini and/or >5%

*Conduction disorders:*

- Asystole >3sec (including conversion pauses)
- New first degree AV block with PQ > 300 msec
- Progression first degree AV block with 15%
- 2nd degree AV block Mobitz type I and II
- 3rd degree AV block
- Any SA block

*Other:*

- (near-)Syncope recurrence
- Unexplained fall with injury
- All cause death
- Cardiovascular death

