**Study Design:**

The RISC trial is an investigator-initiated multicentre prospective randomized controlled trial. A total of 640 predefined low- and intermediate-risk syncope patients are randomized to either immediate discharge or discharge after 24 h in-hospital rhythm monitoring (1:1). The trial is powered to claim non-inferiority of immediate discharge with respect to (non-)fatal composite safety endpoints, which entail arrhythmic disorders, syncope recurrence, and (cardiovascular)death. Furthermore, healthcare costs and quality of life will be evaluated.

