## Rationale

The current reason for the admission of syncope patients is two-fold. First, admission is considered safe because, in the case of rhythm disorders, immediate treatment can be started. Second, admission for monitoring may provide additional diagnostic value, given the chance of witnessing recurrence during the first hours after the syncopal event.^14^ Therefore, the question posed for intermediate-risk syncope patients is two-fold as well: is it safe to discharge these patients, and does admission provide a diagnostic benefit? If intermediate-risk patients can be safely discharged but might profit from rhythm observation, the solution of immediate discharge combined with immediate ambulant Holter monitoring could greatly reduce healthcare costs. Similarly, if there is no diagnostic yield, ambulant Holter monitoring could be omitted as well.

Therefore, we propose the RISC trial to investigate the safety of immediate discharge and the clinical benefit of ambulatory Holter monitoring in low- and intermediate-risk syncope patients. Furthermore, it evaluates the true healthcare cost benefit, the effect on the quality of life, the societal costs, and healthcare burden from a patient perspective. Additionally, we aim to investigate the diagnostic efficacy of immediate rhythm observation and, if apparent, the optimal duration of ambulatory Holter monitoring. The RISC trial, therefore, aims to determine whether immediate discharge with or without ambulatory Holter monitoring is safe and if it is a clinically and economically appropriate alternative to 24-h in hospital cardiac rhythm monitoring in pre-defined low- and intermediate-risk syncope patients.

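### The primary safety composite gives incidental Holter ectopy, not required to be new, the same weight as death and syncope, and no serious-event composite is reported beside it

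*Protocol article*

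**What the plan says.** The Endpoints section calls the composite the primary safety endpoint, evaluates it 24 h after randomization, and refers to Appendix B for all definitions. Among the qualifying events in Appendix B are:

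- "Any atrial tachycardia (sustained or non-sustained ≥ 3 consecutive complexes")
- "Premature Atrial Complex (PAC): >2 doublets or >2 episodes of 3 s duration of bi- or trigemini and/or >5" per cent, with the same thresholds for ventricular premature complexes
- any non-sustained ventricular tachycardia, Mobitz I block and any SA block

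These stand in one list with ventricular fibrillation, third-degree block, syncope recurrence and death. In that list atrial fibrillation must be de novo, and first-degree block must be new or have progressed. Ectopy, runs and SA block carry no such condition.

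Under Randomization and Holter monitoring, both arms receive the same ambulatory device from randomization. The Rationale explains the role of admission thus: "admission is considered safe because, in the case of rhythm disorders, immediate treatment can be started".

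The Statistical considerations state: "we anticipate an event rate of 18% in both arms". The margin is 9 percentage points, half of that rate. Under Data analysis and bias, non-inferiority is declared when the 95% Farrington–Manning interval for the difference in the composite excludes 9%. The secondary endpoints in the Endpoints section include no composite of serious events.

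**The concern.** A non-inferiority test on a composite is informative about safety only as far as the components respond to the strategy under test. Whether a patient shows three atrial doublets in 24 h is unlikely to depend on being at home or on a ward. The Rationale claims that admission lets a rhythm disorder be treated, not that it prevents ectopy. With the same recorder in both arms, such findings should occur at about the same rate in each.

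Events of that kind fill up the 18% without separating the arms. A 9-point margin that is half of the total can be a large multiple of the part made up of serious events. In a non-inferiority trial, dilution towards no difference favours the claim. At stake is whether a positive primary result supports the conclusion the article seeks, that immediate discharge is feasible and safe.

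**Working it through.** **Inputs.** From the Statistical considerations: 18% in both arms, margin 9 points, 640 patients, 10% loss, 80% power. One-sided alpha is 0.025; it is printed there without its decimal point, but Data analysis and bias confirms 2.5%. Allocation is 1:1. The serious-event share of the 18% is not given, so it is an assumption, varied here from 0.5% to 9%.

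**1. The plan's own sample size.** n per arm = (1.96 + 0.8416)² × 2 × 0.18 × 0.82 / 0.09² = 7.849 × 0.2952 / 0.0081 = 286.05, so 287. Dividing by 0.90 gives 319 per arm, 638 in total, against 640 stated. The 6% example also reproduces: 7.849 × 0.2952 / 0.0036 = 643.6, so 644 per arm. The sample size arithmetic is sound.

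**2. Power of the planned test.** 640 less 10% leaves 288 per arm. Summing exact binomial probabilities over all outcomes in which the Farrington–Manning statistic for a 9-point margin is below −1.96 gives 79.9% at 18% v 18%.

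**3. Doubling the serious events.** Let s be the comparator's serious-event rate, and keep the comparator composite at 18%. In the discharge arm serious events become 2s and everything else is unchanged. There are two ways to combine the rates:

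- Addition (no overlap): discharge composite = 18% + s.
- Independence: background b = 1 − 0.82/(1 − s); discharge composite = 1 − (1 − b)(1 − 2s). For s = 3%: b = 15.46%, composite = 1 − 0.8454 × 0.94 = 20.54%.

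The exact probability of declaring non-inferiority, 288 per arm, is:

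| Serious rate, comparator → discharge | Discharge composite (addition / independence) | Declared non-inferior (addition / independence) |
|---|---|---|
| 0.5% → 1% | 18.5% / 18.4% | 75% / 76% |
| 1% → 2% | 19.0% / 18.8% | 69% / 71% |
| 2% → 4% | 20.0% / 19.7% | 57% / 61% |
| 3% → 6% | 21.0% / 20.5% | 44% / 50% |
| 4% → 8% | 22.0% / 21.4% | 32% / 39% |
| 5% → 10% | 23.0% / 22.3% | 22% / 29% |
| 6% → 12% | 24.0% / 23.2% | 14% / 20% |
| 9% → 18% | 27.0% / 26.1% | 2.5% / 4.5% |

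**4. The same in observed counts.** With 52 comparator events among 288 (18%), the test passes with up to 59 in the discharge arm.

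- Serious events 6 → 12, all else equal: 58 v 52, one-sided p = 0.018, declared.
- 7 → 14: 59 v 52, p = 0.023, declared.
- 9 → 18: 61 v 52, p = 0.038, not declared.

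**5. What a serious-event interval would deliver.** The 95% half-width for a difference is 1.96 × √(2s(1 − s)/288). At s = 2% this is 1.96 × √(0.0392/288) = 2.3 points; at 3%, 1.96 × √(0.0582/288) = 2.8 points.

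**6. Why the primary endpoint is not replaced.** A serious-only primary endpoint with the article's relative margin of 1.5 would need, including 10% loss, about 13,816 patients at a 1% rate, 6,838 at 2%, 4,514 at 3% and 2,654 at 5%.

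**The case against.** The strongest objection is that the result depends on a split the article does not give. The 18% rests on cited studies and institutional data that are not shown. If serious events make up 5 points or more, a doubling passes 29% of the time or less; at 9 points it passes at about the nominal error rate. This stands, and it is why the whole range is shown. The article's description points to a low share: high-risk patients are excluded, highly likely autonomic syncope is eligible, the window is 24 h, and the population's risk is said to be close to normal. That is a pointer, not a figure.

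Equal ectopy by arm is likewise an inference. Treatment begun during admission could alter later arrhythmia within the 24 h. Central review of potential endpoints is planned, but the article states no criterion of seriousness or novelty for it.

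Component tables by arm are usual analysis-plan content, and their absence here is not criticised.

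A reader might go further in three ways that the documents do not support:

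- **That the margin lets serious events rise from 3% to 12%.** This is 27% v 18%, the boundary of the null hypothesis, where the test passes only 2.5% of the time.
- **That only atrial fibrillation and first-degree block must be new.** Appendix C also marks atrial flutter as new, and one AV-block row covers new first-, second- or third-degree block.
- **That a patient with known Mobitz I is automatically an event.** The separate second-degree row in Appendix C has no such qualifier, so the text is ambiguous, and Table 1 is not available to show whether such patients are eligible.

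**Conclusion.** The point holds as a conditional design weakness. The article establishes that incidental ectopy, short runs and SA block count equally with the gravest events without having to be new, and that non-inferiority is decided on the total alone. If serious events are 1–3% of patients and the other components are equal by arm, a true doubling passes 44–71% of the time, against 80% with no difference at all. The composite would then say little about serious harm. At 5% and above, the test gives reasonable protection against a doubling.

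It does not follow that non-inferiority will be declared while serious events double: at an assumed 3%, failing to declare it is at least as likely. Nor is the sample size wrong, since 640 reproduces. The defect lies in what the 18% may contain and in the lack of any pre-specified serious-event result beside it.

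**What to change.** Keep the primary test, margin and sample size.

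1. **Serious-event composite.** Add one to the secondary endpoints, drawn from Appendix B items. An example is all-cause death, syncope recurrence, unexplained fall with injury, sustained VT or VF, Mobitz II or third-degree AV block, and asystole over 3 s. The event committee should settle the list before any results by arm are seen. Report the risk difference with 95% CI beside the primary result.
2. **Wording of the conclusion.** State that any conclusion that discharge is safe refers to both results.
3. **Reconcile the definitions.** The Endpoints section omits premature complexes and first-degree block, which Appendix B counts. It includes bradycardia, which Appendix C marks as not an endpoint. Appendix B counts atrial runs of at least three complexes, whereas Appendix C requires more than three. Say for each rhythm finding whether it must be new.

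The cost is mainly wording, because the items are already recorded and potential endpoints are centrally reviewed. The data must separate Mobitz I from Mobitz II and syncope from near-syncope, which Appendix B places on shared lines. The downside is precision: at 2–3% per arm the half-width is about 2.3–2.8 points, so the interval cannot by itself exclude a doubling and should be reported as such.

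A repeat of the primary analysis that leaves out findings documented before randomization is optional. It would have little to work with, since a 12-lead ECG but no baseline Holter is described.
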